## Abstract

**Importance:**

Chronic low back pain (CLBP) is a global health problem with significant clinical, social, and economic challenges. Over 80% of CLBP cases are non-specific (CNLBP), causing the highest number of years lived with disability. People with CNLBP often have comorbidities such as overweight or obesity, which negatively impact symptoms and treatment outcomes.

**Objective:**

The objective is to evaluate whether a lifestyle intervention combining diet, physical activity, and evidence-based physical therapy can reduce pain in individuals with CNLBP and comorbid overweight or obesity.

**Design:**

This is an international multicenter triple-blinded randomized controlled trial (RCT).

**Setting:**

The trial will be conducted in Belgium and Switzerland, with interventions delivered in hospitals (ambulatory care) and outpatient private practices.

**Participants:**

In total, 252 adults will be included and randomly assigned to 1 of 2 treatment arms.

**Interventions:**

The control intervention includes Pain Neuroscience Education and Cognition-Targeted Exercise Therapy. The experimental group receives the same intervention supplemented with a Behavioral Weight Reduction Program.

**Main Outcomes and Measures:**

The primary outcome is pain intensity (assessed using the Brief Pain Inventory). Secondary outcomes include other pain-related outcomes, body composition measures, energy balance related behavior, medical consumption, indirect health-related costs, and quality of life. Assessments will occur at baseline, post-intervention, and at 3-, 6-, 9-, and 12-months follow-up.

**Conclusion:**

This study is the first international multicenter RCT integrating a lifestyle approach into evidence-based physical therapy for people with CNLBP and comorbid overweight or obesity. It will assess whether addressing comorbid overweight or obesity enhances pain reduction and other health outcomes in this population.

**Relevance:**

The results will push the field forward, leading to new knowledge about the (cost-)effectiveness of this approach, which will provide key insights for different stakeholders, help optimizing therapy guidelines and individualized care for people with CNLBP and comorbid overweight or obesity.

## INTRODUCTION

Among musculoskeletal disorders, low back pain (LBP) causes the highest overall burden and years lived with disability globally, resulting in tremendous direct and indirect health care costs (eg, productivity loss).^1^ In about 30% of the LBP cases, pain lasts more than 3 months, and transitions into chronicity (ie, chronic low back pain [CLBP]).^2^ In 80% of cases, CLBP is non-specific in nature (ie, chronic non-specific low back pain [CNLBP]) and is known for its very high incidence and prevalence rates ranging from 3.9% up to 93%.^3^^,^^4^ People with CNLBP often show comorbidities such as overweight and obesity, with different studies showing a close interaction between CNLBP and body composition.^5–8^ Indeed, pain intensity and disability have a dose–response relationship with body mass index (BMI), waist circumference, body fat percentage, and fat mass.^9^ Moreover, overweight and obesity itself are leading risk factors for general disability and increased mortality, resulting in wide-reaching financial consequences.^10–12^

Currently, pain neuroscience education (PNE) and cognition-targeted exercise therapy (CTET) have been shown to be more effective than general education and exercise in managing CNLBP.^13–16^ PNE increases patients’ knowledge of the underlying mechanisms of pain, helping them to reconceptualize pain as less threatening.^17–19^ CTET is based on motor control training and follows a time-contingent approach.^20^ It systematically progresses exercises toward more feared or avoided movements, aiming to break the cycle of pain-related fear, while incorporating therapist-guided discussions to address the patient’s perceptions, concerns, and unhelpful beliefs, thereby reinforcing PNE principles.^13^^,^^15^^,^^20^ Together, PNE and CTET have demonstrated greater reductions in pain and disability, as well as improvements in function in adults with CLBP compared to general exercise and education or exercise alone.^13^^,^^21^^,^^22^

Moreover, overweight and obesity are increasingly recognized as a plausible therapeutic target for people with CNLBP.^23^ Despite their close interaction, few treatment programs for people with CNLBP take overweight or obesity into account and a systematic review identified the need for well-designed, high-quality trials to examine this combined treatment in adults with CLBP and overweight or obesity.^24^^,^^25^ One small-scale proof-of-concept study involving 46 individuals with obesity and CLBP demonstrated that a non-surgical weight loss program, focusing on diet and exercise, not only led to weight loss but also decreased pain (in 48% of participants) and disability (in 70% of participants).^25^ While the findings are compelling, the study’s pre-experimental design limits the ability to draw causal conclusions. Also, in other populations like adults with knee osteoarthritis and overweight or obesity, different high-quality trials showed better outcomes in pain and function when exercise therapy and a dietary change was combined, compared to exercise therapy or dietary changes alone.^26–29^

Given the lack of high-quality studies evaluating the added value of weight management in persons with CNLBP, and the available evidence for its potential in other populations, this article describes the protocol for an international multicenter randomized controlled trial (RCT), which investigates the added value of a lifestyle intervention including a Behavioral Weight Reduction Program (BWRP) to the current best evidence care (ie, PNE and CTET) in people with CNLBP and overweight or obesity. The duration of the intervention for both treatment arms is 14 weeks.

The primary objective of this study is to examine whether adding a BWRP to PNE and CTET compared to PNE and CTET alone, results in less pain in people with CNLBP and overweight or obesity at 12 months follow-up. Secondary objectives focus on the effects in terms of (1) other pain related outcomes, (2) body composition, (3) energy balance related behavior, (4) medical consumption, (5) indirect health costs, and (6) quality of life.

## METHODS

### Study Design

This is the study protocol of the back pain, overweight, obese, weight loss study, a multicenter randomized controlled trial designed to assess the effectiveness of a lifestyle intervention in individuals with overweight or obesity and CNLBP. The international multicenter RCT is conducted in collaboration with the Vrije Universiteit Brussel (Belgium), the Bern University of Applied Sciences (Switzerland), and the University of Applied Sciences and Arts of Southern Switzerland. The protocol follows the Standard Protocol Items: Recommendations for Interventional Trials guidelines^30^ and the Consolidated Standards of Reporting Trials Statement.^31^ The trial was prospectively registered on ClinicalTrials.gov (NCT05811624) in April 2023 and recruitment started in May 2023. To date, 79 patients are included. Figure 1 shows the study flow beginning with an interested participant to the final follow-up assessment.

**Figure 1 f1:**
[figure not shown]
Flow Diagram of the Study. Abbreviations: BMI = Body Mass Index; BWRP = Behavioral Weight Reduction Program; CTET = Cognition-Targeted Exercise Therapy; PNE = Pain Neuroscience Education.

### Participants

In total, 252 participants with CNLBP and overweight or obesity will be recruited (126 per country). Table 1 depicts a detailed overview of the inclusion and exclusion criteria for participants, study centers, and physical therapists performing the intervention.

**Table 1 TB1:** Eligibility Criteria*^a^*

**Criteria for Participants**	
**Inclusion Criteria**	**Exclusion Criteria**
Good knowledge of German/Dutch language (verbal and written)	Severe underlying diseases (eg, diagnosed metabolic disease, diagnosed diabetes, diagnosed cancer, ongoing diagnosed severe depression, diagnosed cognitive impairment, diagnosed eating disorder)
Adults between 18 and 65 years	Being pregnant or given birth in the preceding year, breastfeeding
CNLBP defined according to the NIH Pain Consortium Research Task Force (RTF)^32^: Constant non-specific LBP pain ≥3 months or half of the days in the last 6 months	Specific spinal pathology (eg, disc herniation with clear neuropathic component, spinal stenosis, spondylolisthesis, spinal infection, spinal fracture, malignancy)
Leg pain <7/10 on the NPRS	Dietary or exercise intervention in the last 6 weeks or currently ongoing
BMI overweight ≥25-29.9 kg m^−2^ or obese ≥30-39.9 kg m^−2^^33^	BMI ≥ 40 kg m^−2^
Continuation of usual care 6 weeks prior and during study participation (ie, steady state in usual care)	Healthy body fat %^34^ and healthy WHR (sex and age adjusted)^35^
Signed informed consent	In clarification of invalidity payments
**Criteria for Physical Therapists and Therapy Centers**	
**Inclusion Criteria**	**Exclusion Criteria**
Bachelor of Science in Physical Therapy for Swiss physical therapists and Master of Science in Physical therapy for Belgian physical therapists	Treatment centers only having open treatment rooms, which cannot guarantee privacy and treatment blinding
Fluent English and German or Dutch speaker	
Participation and completion of the trainings provided by the study personnel	
Availability of at least 1 therapist for the experimental and 1 for the control group per treatment location Hospital or private practice setting Treatment rooms that can be closed Similar equipment among the locations/treatment rooms Flexible treatment schedules of physical therapists to guarantee the blinding of participants (eg, no parallel sessions causing participants to see each other in the waiting room)	

^a^
Abbreviations: BMI = Body Mass Index (kg m^−2^); CNLBP = chronic non-specific low back pain; LBP = low back pain; NIH = National Institutes of Health; NPRS = numeric rating scale for pain (0 to 10); WHR = waist-to-hip ratio.

### Recruitment and Informed Consent

Different recruitment strategies will be implemented to reach a diverse group of eligible participants (see Suppl. Material 1). Interested people can apply for study participation on the project website, by directly filling out a first screening questionnaire (Microsoft Forms; Microsoft Corp; Redmond, WA, USA) or by contacting the study team via email or telephone for further information. If the first contact occurs via mail or telephone, the link for the screening questionnaire will be sent afterwards. Participants will be screened for eligibility by research team members, who are not involved in the randomization process or the interventions. All eligible participants will receive an informed consent form (ICF) and are instructed to read it carefully. The ICF will be signed at the beginning of baseline testing, once potential study participants have been given sufficient time to re-read the informed consent and to ask questions. Overweight and obesity were identified based on the Lancet Diabetes & Endocrinology Commission’s recommendation to use a direct body fat measurement or at least 1 anthropometric measurement (eg, waist-to-hip ratio) in addition to BMI.^36^ Therefore, final inclusion will only be confirmed during baseline testing when BMI, body fat percentage, and waist-to-hip ratio are measured on-site. These measurements could lead to exclusion when a participant demonstrates healthy ranges despite having a high BMI, which is possible in athletic individuals and is a known limitation of using BMI as a single parameter to determine overweight or obesity.^36^^,^^37^

### Randomization and Blinding

Patients will be randomly assigned to either the experimental or control group, utilizing a computer-generated number sequence. Randomization is stratified for weight category (overweight/obesity), sex (female/male), country (Belgium/Switzerland), and therapy center. The randomization lists with patient numbers and group allocation will only be accessible by an independent researcher. This researcher coordinates all appointment times with the therapist and assessors in both countries to avoid contact between assessors and therapists, assuring assessors’ blinding. In addition, the participants and the statistician will be blinded for allocation. For participants, this is possible as only a vague description of the therapy is provided in the ICF. Moreover, the therapists providing the experimental treatment are not involved in providing the control intervention and vice versa. The interventions will take place at different times during the day to avoid contamination between groups, and patients will not see each other at the hospital or private practice waiting rooms, nor at the university for measurements. Furthermore, blinding success for both patients and assessors will be evaluated by asking whether they believe the patient received the experimental or control intervention, along with their level of certainty (0% being very unsure, 100% being absolutely sure about the group assignment).

### Settings and Procedures

#### Location Settings

All on-site assessments (baseline, post-intervention, 1-year follow up) will be performed at Vrije Universiteit Brussel, Belgium or Bern University of Applied Sciences, Switzerland. The intervention will be conducted in hospitals (ambulatory care) or private practice rooms of the respective physical therapists in each country.

#### Intervention

Both treatment arms will include 18 sessions spread over a 14-week period, including 17 one-on-one sessions and 1 asynchronous session, where online material will be provided. All treatment sessions will have a duration of approximately 30 minutes and will take place at the cabinet of the respective therapists in Switzerland or in Belgium. If illness or vacation cause absences, participants and therapists are requested to catch up the missed sessions within the 14-weeks’ timeframe if possible. Final number of attended sessions will be recorded. Both treatment arms are organized equally: all participants will receive 3 sessions of PNE in the first 2 weeks, following 15 sessions of CTET (including integration of BWRP for the experimental group) in the remaining 12 weeks. The BWRP intervention will include a lifestyle approach, implying grading daily physical activity and exercise levels alongside of a change in diet to reduce weight. The structure of the sessions and the detailed content of the interventions can be found in Suppl. Material 2 and 3. After the post-intervention measurement, participants will be allowed to receive concomitant care (eg, physical therapy, nutritionist counseling, medication change), which will be monitored with the Medical Consumption Questionnaire during the follow-up period.^38^ Every 3 months, participants will receive and email invitation to complete the follow-up questionnaires via REDCap software (Vanderbilt University, Tennessee, USA) and to fill out a food diary at the 3-month (T2) and 6-month (T3) follow-up (see Table 2). To ensure data completeness, automated reminders will be set up through REDCap, and assessors will contact participants if data remains missing after a reasonable period. After the last follow-up assessment at 12 months (T5) and therefore completion of the study, participants will receive a total remuneration of €120 as travel reimbursement.

**Table 2 TB2:** Overview of the Time Schedule of All Assessments*^a^*

**Timepoint**	**Study Period**					
	**Baseline**	**Post-Intervention**	**Follow-Up**			
	**T0**	**T1**	**T2**	**T3**	**T4**	**T5**
**Participant Characteristics**						
**Socio-demographic** Birth year Sex Marital status Occupation Employment status Education Sports (mean duration/week in min) Duration of CNLBP (month) Disease or comorbidities Special diet (eg, vegetarian, vegan, nutrition supplements, food intolerances or allergies)	X					
**Primary Outcome**						
**Pain intensity (BPI)**	X	X	X	X		X
**Secondary Outcome**						
**Pain-related outcomes** Pain distribution (pain drawing)	X	X				X
Pain interference (BPI) Kinesiophobia (TSK) Fear avoidance beliefs (FABQ)	X	X	X	X		X
**Body composition and anthropometrics** Height (SECA stadiometer)	X					
BMI (kg m^−2^) Weight (Tanita) Body fat and fat free mass (TANITA analyzer) Body fat distribution (WC, HC, WHR) Subcutaneous adipose tissue thickness (ultrasound) Muscle thickness (ultrasound)	X	X				X
**Energy balance related behavior** Dietary intake (3-day food diary)	X	X	X	X		X
Sleep quantity (Fitbit Sense) Sleep quality (PSQI)	X	X				X
	X	X	X	X		X
Rest activity cycles (Fitbit Sense) Continuous physical activity (Fitbit Sense)	X	X				X
**Costs** Medical consumption (iMCQ) Indirect health costs (iPCQ)	X	X	X	X	X	X
**Quality of life** Quality of life (EQ-5D-5L)	X	X	X	X	X	X
**Additional Outcomes**						
Therapy adherence		X				
Blinding—group allocation guess						X

^a^
Abbreviations: BMI = body Mass Index; BPI = Brief Pain Inventory; CNLBP = Chronic Non-specific Low Back Pain; EQ-5D-5L = EuroQol 5D-5L questionnaire; FABQ = Fear avoidance belief questionnaire; HC = hip circumference; iMCQ = Medical Consumption Questionnaire; iPCQ = Productivity Cost Questionnaire; PSQI = Pittsburgh Sleep Quality Index; T0 = baseline, 1 week before therapy starts; T1 = post-intervention measurement, 1 week after the 14-week trial; T2 = 3 month follow-up (online); T3 = 6 month follow-up (online); T4 = 9 month follow-up (online), T5 = 12 month follow-up (onsite); TSK = Tampa Scale of Kinesiophobia, WC = waist circumference; WHR = waist-to-hip ratio.

#### Training of Therapists

All sessions will be provided by specially trained physical therapists. The training of PNE and CTET will be provided to all therapists, but only experimental therapists received the BWRP training to avoid treatment contamination. Therapists will not be allowed to switch groups after the training, but the content of the BWRP will be available for the control therapists at the end of the trial. The participants will be treated by the same physical therapist during the whole 14-week period. The training of the therapists will follow standardized intervention manuals (see Supplementary Material 4).

#### Therapy Adherence, Adverse Events, and Discontinuation of the Trial

Therapists will be instructed to document the course of treatment as required by their workplace guidelines. After a participant completes the 14-week therapy period, the therapist will be asked to complete a questionnaire on therapy adherence, compliance, and any adverse events (see Suppl. Material 5). No serious adverse events are expected, and the trial is rated as low-risk category by the ethical committee. Nevertheless, in case of an adverse event, physical therapists will be advised to inform the research team immediately. Furthermore, discontinuation of the trial is considered unlikely. However, if a female participant becomes pregnant or a severe adverse event occurs, participation will be discontinued. In both countries, the principal investigators must inform the respective ethics committee about any adverse events as quickly as possible or within a timeframe of 7 days. Additionally, an annual report on safety, adverse events, and the general progression of the clinical trial will be submitted to the respective ethics committee.

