#### Statistical Analysis Plan

Prior to the analyses, visual inspection for assessing data plausibility will be performed, while the normality assumption will be checked using Q-Q-plots**.** Missing values will be checked for randomness by performing a logistic regression analysis, modeling the probability of missingness against baseline characteristics. If no significant associations are found, missingness will be assumed to be at random**.** Independent samples *t*-tests (for continuous variables) and chi-square tests (for categorical variables) will be performed at baseline to check whether the randomization was successful. If not, variables for which this was not the case will be included as confounders in the main analyses after the direction of the relationship was established using directed acyclic graphs (DAGs).^69^ Drop-out analysis will be performed using independent samples *t*-tests and chi-square tests on the baseline data, while the amount of and reasons for drop-out (participants are asked to give their reasons of withdrawal) will be compared between the experimental and control condition. This procedure will allow us to check whether differential drop-out (and thus attrition bias) is present. Again, variables subject to selection bias will be included as confounders (when identified as such by the DAGs) in the main analyses. General(ized) linear mixed modelling will be performed in R (RStudio version 1.1.383) to evaluate and compare (long-term) therapy effects between the experimental and control intervention. Both the distribution of the outcome measure and residual distributions will be checked for normality using Q-Q-plots. To account for clustering effects (ie, participants will be measured repeatedly, clustered within different hospitals or therapeutic settings), a multilevel model will be constructed, including three levels: (1) repeated measures, (2) clustered within the individual, and (3) clustered within a hospital or other therapeutic setting. This technique is particularly well fitted to analyze repeated measures over time in a hierarchical structure including missing values.^70^ To minimize issues related to multiple testing, contrast testing within the generalized linear mixed model framework will be applied. A priori defined contrasts between the groups will be tested using the R package “multcomp” and the function “glht.” Statistically significant differences will be defined at alpha level .05, and the effect size as well as clinically significant differences will be determined. In addition, numbers needed to treat will be calculated, after transforming the outcome to a binary variable, in analogy with previous research.^71^ Analyses will be performed based on the intention-to-treat principle. Afterward, per protocol analyses will be performed (as a form of sensitivity analysis) to evaluate the effect of therapy adherence and compliance.

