There are some limitations to this study. A relatively high drop-out rate of 25% is expected due to the combination of education with exercise therapy, plus a weight reduction program. However, this is accounted for the sample size calculation, and efforts will be made to reduce drop-out. Additionally, the BWRP will be delivered by physical therapists without established experience in delivering this intervention. Yet, available training protocols, treatment manuals, and feasibility checks of therapy sessions should ensure highest treatment quality. Although some sociodemographic factors will be collected, data on ethnicity will not be included, which limits the ability to explore ethnic disparities across intervention groups and may impact the ability to fully assess the success of the randomization process. Nonetheless, the randomization procedure is assumed to deliver balanced intervention groups for any (un)measured variable.

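### As worded, the therapist form on adherence, compliance and adverse events is requested only once a participant completes 14 weeks, so early stoppers need not have one

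*Protocol article*

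**What the plan says.** The Methods section on therapy adherence, adverse events and discontinuation describes one questionnaire and when it is requested: "After a participant completes the 14-week therapy period, the therapist will be asked to complete a questionnaire on therapy adherence"; the same form also covers compliance and adverse events. Table 2 fits this timing. Under additional outcomes, the row "Therapy adherence" has a single mark, at T1, one week after the 14 weeks end.

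The same Methods section gives a second route for harms: "in case of an adverse event, physical therapists will be advised to inform the research team immediately". It also has therapists keep treatment notes under their own workplace rules, and it has the principal investigators report adverse events to the ethics committee, with an annual safety report. It then states that "if a female participant becomes pregnant or a severe adverse event occurs, participation will be discontinued".

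Two other sections matter. The Intervention section says "Final number of attended sessions will be recorded", with no condition that therapy was completed. The Statistical Analysis Plan section says that "per protocol analyses will be performed (as a form of sensitivity analysis) to evaluate the effect of therapy adherence and compliance", and that the amount of and reasons for drop-out will be compared between arms.

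**The concern.** The form is the only instrument the article describes that asks about adverse events, and the only stated source of a compliance rating. Its trigger is an event that early stoppers do not reach. They are also the participants in whom a poorly tolerated exercise or diet programme would be most likely to show. If the trigger is followed literally, events are solicited from completers and merely volunteered for the rest.

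Two things are at stake. The frequency of adverse events, which feeds the annual safety reports and any harms table, may come out too low. And the planned per-protocol analysis, which is meant to address both adherence and compliance, would lack the compliance rating for some of the least adherent participants.

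The plan expects appreciable drop-out. The limitations paragraph of the Discussion says: "A relatively high drop-out rate of 25% is expected due to the combination of education with exercise therapy, plus a weight reduction program".

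**Working it through.** The article states no figure on this point that could be reproduced. The check is a comparison of the text, followed by a gauge of scale.

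**1. What is held for each kind of participant, on the literal wording**

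| Information | Completes 14 weeks | Stops earlier |
|---|---|---|
| Solicited adverse-event question (therapist form) | yes | no trigger stated |
| Immediate report by therapist (unsolicited) | yes | yes |
| Routine treatment notes | yes | yes, up to stopping |
| Attended sessions | yes | yes |
| Therapist-rated adherence and compliance (same form) | yes | no trigger stated |
| Reason for withdrawal | not applicable | asked on withdrawal from the trial |

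The gap is confined to the two rows that depend on the form. The discontinuation rule in the same section makes it concrete: a participant discontinued during therapy for a severe adverse event need not reach the point at which the adverse-event form is requested.

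**2. How many participants**

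Inputs from the Sample Size Calculation section: N = 252 and 25% drop-out across 12 months. Expected drop-outs = 0.25 × 252 = 63. The share falling before week 14 is not given, so it is varied as an assumption *s*; participants without a form = 63 × *s*.

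- *s* = 25%: 15.75, about 16 (6% of 252)
- *s* = 50%: 31.5, about 32 (12.5%)
- *s* = 75%: 47.25, about 47 (19%)
- *s* = 100%: 63 (25%)

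Drop-out from the trial is not the same as stopping therapy. Someone may stop therapy and still answer follow-up questionnaires, so these figures indicate scale and are not bounds.

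**3. What it could do to adverse-event frequency**

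All risks here are assumptions. Let *d* be the proportion stopping early, *a* the event risk in completers and *b* the risk in early stoppers. True risk = (1 − *d*)*a* + *d b*. The forms alone, among those who have one, show *a*. The shortfall is *d*(*b* − *a*). Take *a* = 10%.

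- *b* = 10%, any *d*: shortfall 0.
- *b* = 30%, *d* = 6.25% in both arms: true 0.9375 × 0.10 + 0.0625 × 0.30 = 11.25%, against 10% shown.
- *b* = 30%, *d* = 25% in both arms: true 0.75 × 0.10 + 0.25 × 0.30 = 15%, against 10% shown. The arm difference is 0 both in truth and on the forms.
- *b* = 30%, *d* = 30% experimental and 20% control: true 0.70 × 0.10 + 0.30 × 0.30 = 16% against 0.80 × 0.10 + 0.20 × 0.30 = 14%. The true difference is 2 points; the forms show 0.
- *b* = 50%, same stopping rates: true 0.07 + 0.15 = 22% against 0.08 + 0.10 = 18%. The true difference is 4 points; the forms show 0.

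These cases count the form alone. Every event that reaches the team through an immediate report narrows the shortfall, and complete immediate reporting would remove it.

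**The case against.** The strongest reply is that *completes* may only fix the time: the form is filled in when the 14-week window ends, whoever attended. A form about adherence and compliance sits oddly with a completers-only rule, nothing says it is withheld from early stoppers, and neither the form (Supplementary Material 5) nor the therapist manuals are shown. This is a fair reading, and it is why the point concerns the wording and not a demonstrated loss of data. It does not remove the point. The article ties the request to the participant completing therapy and gives no other trigger, and the same short amendment settles either reading.

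A reader might infer something stronger: that harms and adherence in early stoppers go unrecorded, and that the comparison of harms between arms is therefore biased. The document does not support this.

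- Immediate reporting of adverse events applies to every participant at any time. It is unsolicited and may miss milder events, but it is not nothing.
- Attended sessions are recorded without a completion condition. Someone who stops at week 5 can be classed as non-adherent on attendance alone, so the per-protocol analysis loses the compliance rating and not the basic classification. That analysis is a sensitivity analysis in any case; the main analysis is by intention to treat.
- No between-arm comparison of adverse events is specified. They are not an outcome in Tables 2 or 3 or in the analysis section.
- The 25% drop-out is one figure for the whole trial. The article links it to the combined programme, and only the experimental arm receives the weight programme, so more early stopping there is plausible. But no rate by arm is given, and the planned comparison of drop-out would show an imbalance.

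**Conclusion.** The point stands in a limited form. Read as written, the solicited form covers participants who finish 14 weeks and need not exist for those who stop. For the latter, adverse events rest on unsolicited reports and treatment notes, and adherence rests on a session count.

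Understated adverse-event frequency is a risk. It requires early stoppers to have more events than completers and immediate reporting to miss some of them. Bias between arms additionally requires stopping rates, early-stopper risk or reporting to differ by arm, and the document establishes none of these. The number affected is unknown; 16 to 47 of 252 rests on the assumption that 25% to 75% of the expected drop-outs occur during therapy. The primary pain analysis is not touched.

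This is an inexpensive improvement to a data-collection rule. It is worth making while the trial is running, because an analysis plan cannot recover a rating that was never requested.

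**What to change.** In the section on therapy adherence and adverse events, and in the therapist manual, state that the questionnaire is requested when the participant reaches the end of the 14 weeks or stops therapy for any reason, whichever comes first. Require it for every randomised participant who attended at least one session, and adjust the Table 2 entry so that it is not tied to T1 alone. State that adverse events will be reported by arm for all randomised participants, with the number lacking a form shown.

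The existing form is used and no treatment or discontinuation rule changes. The cost is a short amendment and a few minutes of therapist time per early stopper. The article reports 79 participants included at the time of writing, which leaves 252 − 79 = 173 for whom the form can be collected prospectively from the start. For participants who have already stopped, it would be completed retrospectively from treatment notes and should be flagged as such.
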